### 5.12.3. Coagulation

Following parameters will be determined on the predefined study days: aPTT and INR

## 5.13. Urine Drug Screen

Urine drug screen includes tests for illicit substances such as amphetamines, barbiturates, methadone, benzodiazepines, cannabinoids, cocaine and opiates, and is performed at screening visit and at Day -1. Results will be available as source data and will not be recorded within the eCRF.

[figure not shown]

## 5.14. Test for SARS-CoV-2 infection

A test for SARS-CoV-2 infection will be conducted during screening (as close as possible to start of confinement). This test may be repeated if clinically indicated and in accordance with local health care regulations (e.g., if the individuals' infection risk changes and/or if signs and symptoms of an infection are reported).

## 6. Study Treatment

Study drug must be received by a designated person at the study site, handled, and stored safely and properly, and kept in a secured location to which only the investigator and designated assistants have access. Upon receipt, all study drugs should be stored according to the instructions specified on the drug labels. Clinical supplies are to be dispensed only in accordance with the protocol.

Medication labels will be in the local language and comply with the legal requirements in Germany. They will include storage conditions for the drug, but no information about the subject, except for the medication number.

### 6.1. Investigational Product

There are two investigational products, niclosamide in two different formulations. Furthermore, placebo will be administered in Part A and C.

Niclosamide is approved for the treatment of tapeworm infection. Niclosamide is available as 500 mg chewing tablets (Yomesan® from Bayer Vital GmbH).

The new oral solution of Bayer AG is available as a 40 mg/mL solution.

#### 6.1.1. Dose and Time of Administration

Niclosamide will be supplied as oral solution 40 mg/mL and 500 mg chewing tablets.

The chewing tablets must be thoroughly chewed to a fine paste before swallowing with only a small amount of water. However, the tablets can also be ingested after dissolving them in water. The oral solution will be taken with approx. 240 ml of non-carbonated water.

[figure not shown]

### Part A (SAD):

The new oral solution will be administered in ascending doses in cohorts A1 to A3 under fasted condition and compared to placebo. The last cohort will be repeated in the same subject under fed conditions.

Planned doses:

Cohort A1:

- Single dose of 200 mg oral niclosamide solution
- Single dose of matching placebo

Cohort A2:

- Single dose of 600 mg oral niclosamide solution
- Single dose of matching placebo

Cohort A3:

- Single dose of 1600 mg oral niclosamide solution
- Single dose of matching placebo

### Part B (relative bioavailability compared to chewing tablets)

Planned doses:

- Single dose of 1600 mg oral niclosamide solution (highest dose that was tested to be safe and tolerable in Part A) under fed conditions
- Single dose of 2000 mg niclosamide chewing tablets as multiples of 500 mg chewing tablets under fed conditions

Part C (multiple doses of the niclosamide solution)

- Multiple doses of 1200 mg oral niclosamide solution under fed conditions over 7 days
- Multiple doses of 1600 mg oral niclosamide solution under fed conditions over 7 days
- Placebo under fed conditions over 7 days

In all cohorts, study drug will be administered at the study site.

In Part A cohorts, subjects must have fasted overnight for at least 9 hours before study drug intake. Intake of water is not allowed from approximately 2 hours before until approximately 2 hours after study drug intake (except for the non-carbonated water required for study drug intake). Standard lunch will be served within 15 to 30 minutes after the 4-hour PK sampling on Day 1 and in Part B also on Day 3. The lunch should be of the same composition for all subjects on Day 1. The standard lunches should be ingested entirely within 30 minutes. If this is not possible, the approximate percentage of the consumed food should be documented.

A standard snack and a standard dinner will be served approximately 7 and 10 hours postdose, respectively. This snack and dinner should be of the same composition for all subjects.

In the fed dose cohort in Part A (cohort 3) and in Part B and Part C, following overnight fast of at least 9 hours, subjects should start a high fat meal 30 minutes prior to the study drug administration at the study site between 7.30 and 10.00 AM. This meal should contain approximately 800 to 1000 calories and should derive approximately 150, 250, and 500 to 600 calories from protein, carbohydrate, and fat, respectively (according to the FDA guidance for industry). Subjects should consume the entire meal within 30 minutes. If this is not possible, the approximate percentage of the consumed food should be documented. Within 10 minutes after completing breakfast, but no more than 30 minutes from the start of their high fat meal, study drug will be administered with approximately 240 mL of non-carbonated water. Thereafter, subjects should receive standardized meals scheduled at the same time in each cohort of the study.

[figure not shown]

Times of intake of study drug, start and stop times of standard lunch and start and stop times of standard snack and dinner will be recorded on the eCRF.

## **6.2. Method of Assigning Subjects to Treatment Groups**

After written informed consent, subjects meeting all in-/exclusion criteria will be randomized at baseline (Day -1) to one of the different treatment arms:

Randomization numbers will be assigned in ascending, sequential order to eligible patients. The investigator will document the randomization number in the source data sheet and the eCRF.

The randomization list will be kept in safe and confidential custody at the CRO. Only personnel not involved in the study will have access to the list. If one of the single verum cohorts will be stopped for safety reasons, the study will nevertheless be continued with the other study drug. The use of the randomization list will then be adapted in a way that only the randomization numbers of the remaining drug will be used.

## **6.3. Blinding Methods**

Subjects will be randomized to receive either niclosamide or placebo in Part A and C. The treatment is supposed to be double-blinded compared to placebo. Cohort B will be conducted in an open-label design.

## **6.4. Emergency Unblinding by the Investigator**

At any time, the investigator will have access to sealed emergency code break envelopes. At his/her discretion (e.g. in case of an emergency, or any finding that requires unblinding), the investigator may open the envelope decoding the subject's treatment.). This will allow breaking the blinding code for an individual subject without impairing the study as a whole. At the end of the study, all code break information will be removed from the study site.

## **6.5. Storage and Stability**

Drug supplies will be kept in their original packaging and in a secure limited access storage area according to the recommended storage conditions on the medication label. The oral solution will be protected from light.

Details can be found in the pharmacy manual.

# **7. Safety Monitoring**

## **7.1. Definitions**

### **7.1.1. Adverse Events (AEs)**

An Adverse Event (AE) is defined as any untoward medical occurrence in a patient or clinical investigation subject administered a pharmaceutical product and which does not necessarily have a causal relationship with this treatment.

Thus, an AE can be any unfavorable and unintended sign (including abnormal laboratory findings), symptom, or disease temporally associated with the use of an investigational medicinal product, whether or not considered related to it.

[figure not shown]

Pre-existing diseases or symptoms or abnormal laboratory values present upon enrollment are not considered as an AE even when observed during the further course of the study. However, every worsening of a pre-existing condition is to be considered as an AE.

### 7.1.2. Serious Adverse Events (SAEs)

An SAE is any untoward medical occurrence that at any dose:

- Results in death.
- Is life-threatening.

NOTE: The term “life-threatening” in this definition refers to an event in which the subject is at risk of death at the time of the event; it does not refer to an event that hypothetically might cause death if it were more severe.

- Requires or prolongs hospital stay - note that hospitalizations for the following reason should not be reported as SAEs:
  - Treatment on an emergency outpatient basis for an event not fulfilling any of the definitions of a SAE given above and not resulting in hospital admission
- Results in persistent or significant disability/incapacity.
- Is a congenital anomaly/birth defect.
- Is otherwise considered as medically important, e.g. requiring medical or surgical intervention to prevent one of the other outcomes listed in the above definition.

In case the AE fulfills one or several of these criteria, the investigator completes an SAE report form.

### 7.1.3. Suspected Unexpected Serious Adverse Reactions (SUSARs)

Suspected unexpected serious adverse reactions (SUSARs) are defined as any adverse reaction that is classified in nature as serious and which is not consistent with the information about the investigational product set out in the IB. Any unexpected SAE that is considered related to the Drug Product will be reported as a SUSAR.

## 7.2. Assessment Criteria

### 7.2.1. Assessment of Severity

The terms “serious” and “severe” are not synonymous. The term ‘severe’ should be used to describe the intensity (severity) of a specific event; the event itself, however, may be of relatively minor significance (such as severe headache). This is not the same as “serious”, which is based on the existence of one of the above (section 7.1.2) mentioned seriousness criteria.

The severity of an AE is graded according to National Cancer Institute (NCI) Common Terminology Criteria for Adverse Events (CTCAE). In general, this refers to the definitions described in Table 4.

**Table 4 Assessment of severity of an AE according to CTCAE Version 5.0**

| Grade | Clinical description of severity                                                                                                                                                 |
|-------|----------------------------------------------------------------------------------------------------------------------------------------------------------------------------------|
| 1     | Mild ; asymptomatic or mild symptoms; clinical or diagnostic observations only; intervention not indicated.                                                               |
| 2     | Moderate ; minimal, local or noninvasive intervention indicated; limiting age-appropriate instrumental ADL*.                                                              |
| 3     | Severe or medically significant but not immediately life-threatening ; hospitalization or prolongation of hospitalization indicated; disabling; limiting self care ADL**. |
| 4     | Life-threatening consequences ; urgent intervention indicated.                                                                                                            |
| 5     | Death related to AE.                                                                                                                                                      |

ADL: Activities of Daily Living

\*Instrumental ADL refer to preparing meals, shopping for groceries or clothes, using the telephone, managing money, etc.

\*\*Self-care ADL refer to bathing, dressing and undressing, feeding self, using the toilet, taking medications, and not bedridden

### 7.2.2. Relationship and Outcome of AEs

The investigator will evaluate each AE that occurred after administration of the IMP regarding the **relationship** with the administration of the IMP:

**Table 5 Relationship and outcome of AEs**

|              |                                                                                                                                                                                                                                                                                                                                                                 |
|--------------|-----------------------------------------------------------------------------------------------------------------------------------------------------------------------------------------------------------------------------------------------------------------------------------------------------------------------------------------------------------------|
| Related:     | 

There is a reasonable possibility that the event may have been caused by the IMP. A certain event has a strong temporal relationship and an alternative cause is unlikely.

                                                                                                                               |
|              | 

An AE that has a reasonable possibility that the event is likely to have been caused by the IMP. The AE has a timely relationship and follows a known pattern of response, but a potential alternative cause may be present.

                                                                      |
|              | 

An AE that has a reasonable possibility that the event may have been caused by the IMP. The AE has a timely relationship to the IMP; however, the pattern of response is untypical, and an alternative cause seems more likely, or there is significant uncertainty about the cause of the event.

 |
| Non-related: | 

Only a remote connection exists between the IMP and the reported adverse event. Other conditions including concurrent illness, progression or expression of the disease state or reaction of the concomitant medication appear to explain the reported adverse event.

                                           |
|              | 

An AE that does not follow a reasonable temporal sequence related to the IMP and is likely to have been produced by the subject's clinical state, other modes of therapy or other known etiology.

                                                                                                               |
|              | 

There is insufficient or incomplete evidence to make a clinical judgement of the causal relationship.

                                                                                                                                                                                                           |

AE relationship to the study medication will be assessed at the site by the investigator and recorded on the AE page of the eCRF.

When the final causality assessment is unknown and it is uncertain whether or not the IMP caused the AE, then the AE should be handled as related to the IMP for reporting purposes.

As far as possible, each AE should be further evaluated to determine its:

- **Duration** (start and end date, time)
- **Action taken** with respect to IMP (dose interrupted, drug withdrawn, not applicable, unknown) **or** whether other action taken (to be specified, concomitant medication changed, not applicable, unknown)
- **Outcome** (not recovered/not resolved, recovered/resolved, recovering/resolving, recovered/resolved with sequelae, fatal, unknown)

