### **3.3. Stopping Rules for Dose Escalation (Part A)**

#### **Safety stopping rules**

Safety data of all subjects in a given cohort until Day 2 must be reviewed. If one or more of the following criteria is met, dosing will be paused at any time during the study and the SMC will be consulted.

- Occurrence of a serious adverse event (SAE) assessed as related to the IMP in at least one subject.
- Occurrence of severe (Grade  $\geq 3$  based on common terminology criteria for adverse events [CTCAE]) adverse events (AE) assessed as related to IMP in two subjects in the same cohort, independent of within or not within the same system-organ-class.
- Occurrence of relevant (as judged by the investigator) and confirmed safety lab deviations in two or more subjects.

The study may continue after comprehensive review by the SMC if the safety signals obtained are considered not to preclude further dosing within the cohort. Dose escalation of the niclosamide solution will only be performed if the SMC and the Investigator confirm and agree that the current emerging safety and tolerability data support dose escalation.

[figure not shown]

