## 8. Statistical Analysis

All medical terms reported as adverse events (AE) are coded according to the Medical Dictionary for Regulatory Activities (MedDRA) for safety analysis. At least the primary System Organ Class (SOC) as well as the Preferred Term (PT) will be available for the statistical analysis. Incidences of AEs will be summarized by intensity and relationship to the study drug.

Descriptive statistics will be calculated for plasma concentration of niclosamide at each applicable time point specified, and for the derived plasma PK parameters.

The primary PK parameters are  $C_{max}$ ,  $AUC_{last}$  and  $AUC_{inf}$ ,  $C_{8h}$ ,  $C_{12h}$ ,  $C_{24h}$ ,  $T_{1/2}$ .

The food effect evaluation in Part A and the relative bioavailability compared to the chewing tablets in Part B will be performed using a linear fixed effect model containing fixed effects for sequence, treatment, period and subjects within sequence for log-transformed  $C_{max}$ ,  $AUC_{last}$

[figure not shown]

and AUCinf, respectively. Only subjects with evaluable data for both periods. The point estimate of the ratio of geometric means (fed/fasted; oral solution/chewing tablets) will be provided together with a 90% confidence interval

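### Adverse events whose causality cannot be judged are Non-related in Table 5 but handled as related for reporting, and the protocol does not say which applies to the incidence tables

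*Protocol*

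**What the plan says.** Section 7.2.2 of the Protocol has the investigator assess each AE occurring after dosing for its relationship to the IMP and enter the result on the AE page of the eCRF. Table 5 supplies the definitions. It has two labels, Related and Non-related, with three entries each. The Non-related block opens with "Only a remote connection exists between the IMP and the reported adverse event" and closes with "There is insufficient or incomplete evidence to make a clinical judgement of the causal relationship".

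The text under the table sets a rule for the undecided case. If no causal conclusion has been reached and the role of the IMP remains in doubt, "then the AE should be handled as related to the IMP for reporting purposes".

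The relationship category is used in three places:

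- Section 8: "Incidences of AEs will be summarized by intensity and relationship to the study drug". AEs are among the primary endpoints in Section 2.2.1.
- Section 3.3 (Part A), first two pausing criteria: "Occurrence of a serious adverse event (SAE) assessed as related to the IMP in at least one subject", and Grade 3 or higher "adverse events (AE) assessed as related to IMP in two subjects in the same cohort".
- Section 7.1.3, where an unexpected SAE considered related is a SUSAR.

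**The concern.** The last Non-related entry and the sentence under the table describe the same situation: no causal judgement can be made. They give it opposite labels. The sentence limits itself to reporting, but the protocol does not say whether that means only expedited safety reporting or also the reporting of study results in tables. Nor does it say that Table 5 alone governs the tables.

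An investigator who follows Table 5 records an unassessable AE as Non-related, and that value is what Section 8 counts. The same AE may leave the site as related. The incidence of drug-related AEs is then too low by the protocol's own convention, in groups small enough for one subject to matter.

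**Working it through.** No sample-size or error-rate figure in the plan bears on this, so there is nothing to reproduce. The check is a comparison of text, followed by counting.

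**1. The passages side by side**

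| Place | Situation described | Label |
|---|---|---|
| Table 5, last Non-related entry | evidence too thin to judge causality | Non-related |
| Text below Table 5 | causality unknown and uncertain | related, for reporting |
| Table 5, last Related entry | timely relationship, reasonable possibility of causation, untypical pattern, cause uncertain | Related |

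Rows 1 and 2 conflict unless the second is confined to a use that the first does not serve. The protocol does not draw that line. Row 3 is close to row 1 but has added conditions, so it is not the same definition.

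**2. What the recorded category feeds**

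The Section 8 incidences by relationship take the site's classification. Moving events out of Related can only lower the related count in a group, never raise it, so the direction of the effect on related-AE incidence is fixed. This says nothing about the difference between active and placebo, because placebo subjects are classified by the same table.

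**3. Size, by counting**

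Inputs: Part A cohorts have 4 subjects at 3:1, so 3 on active (Section 3.1). Part C dose groups have 4 each (Section 3.1), so 8 on active (Section 8.1). Assume that one subject's only AE is of undeterminable causality. No such event is documented; this is an illustration. The shift is 1/n.

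| Group | Active n | By Table 5 | By the text | Difference |
|---|---|---|---|---|
| Part A cohort | 3 | 0/3 = 0% | 1/3 = 33.3% | 33.3 points |
| Part C dose group | 4 | 0/4 = 0% | 1/4 = 25% | 25 points |
| Part C, both doses | 8 | 0/8 = 0% | 1/8 = 12.5% | 12.5 points |

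If that subject also had another AE classed as related, the subject-level incidence would not move.

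**4. Pausing criteria**

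The first two Section 3.3 criteria depend on relatedness. One SAE of undeterminable causality counts as 0 under Table 5 and as 1 if the text applies, against a threshold of one subject. The third criterion (laboratory deviations) does not use relatedness. The Part C rule for the 1600 mg group in Section 3.4 does not use Table 5; it has its own attribution to the excipient.

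**The case against.** The strongest reply is that the sentence below the table is expressly tied to reporting, and the next section, 7.3, is about reporting AEs, SAEs and SUSARs. On that reading there are two tiers: the site records a Table 5 category, and undeterminable cases are treated as related when safety reports are made. Incidences and pausing criteria would then follow the recorded category without ambiguity. This is a natural reading, but the protocol does not state it. Even if it is right, unassessable AEs are counted as not drug-related in the safety tables, and the clinical data disagree with the reports. The SAE reconciliation in Section 9.7 would not reach non-serious AEs.

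Three stronger conclusions might be inferred, and the document does not support them:

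- *SUSARs would be missed.* SUSAR reporting is the use that the sentence most clearly covers, and it already directs such cases to be handled as related. Section 7.3 also requires an SAE form regardless of causality, and Section 7.3.2 sets a 24-hour limit.
- *Table 5 lets the same AE go into either block.* The Related entry that ends "or there is significant uncertainty about the cause of the event" also requires a timely relationship and a reasonable possibility of causation. The two entries adjoin but do not coincide.
- *Dosing decisions across the trial hang on this.* Only the first two Part A criteria use relatedness, and the rationale for Amendment 2 shows that Part A data had already been evaluated. Section 4.4 withdraws a subject for any SAE or Grade 3 or higher AE, and the committee in Section 3.6 sees all safety data; neither depends on relatedness.

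It is also fair to say that all analyses are descriptive with full listings (Section 8.1), so no hypothesis test turns on the category. A separate SAP could settle how to tabulate. It could not separate unassessable from remote events afterwards if the eCRF field carries only the two labels of Table 5.

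Finally, the disputed row has a blank label cell in the text available. The three-and-three layout, with no third label, supports placing it under Non-related.

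**Conclusion.** The inconsistency stands, in limited form. Table 5 labels AEs of undeterminable causality Non-related, the text below it handles them as related for reporting, and the scope of that rule is not stated. The category that feeds the Section 8 incidences can therefore differ from the one reported, and the effect on drug-related AE incidence is downwards. One affected subject would shift it by the fractions shown above, on the assumption that the subject has no other related AE; nothing in the document shows that such an event occurred. For the two Part A pausing criteria, the conclusion goes no further than that the governing classification is unstated. The point is worth correcting because it touches a primary safety summary and the correction is cheap. It does not call the design into question.

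**What to change.** Take the entry on insufficient evidence out of the Non-related block of Table 5 and give it its own category, such as unassessable. State that this category is counted as related in the Section 8 incidence tables and in safety reporting, which follows the protocol's own sentence. Re-check any AEs already coded under that entry, including those from Part A.

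Separately, the sponsor should reconcile Section 7.2.2 with the first two criteria of Section 3.3 and state which classification applies there. Which one it should be is not a matter for this review.

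The cost is one table row, an eCRF completion note (plus one added option if the field has only two values) and the re-check. The downside is that related-AE incidence may look slightly higher. Keeping the category separate lets a reader see how much of it comes from unassessable events.
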